**Methods:**

Our trial will be a prospective, rater-blinded randomized controlled trial carried out with primary care physicians in the Sahel region of Tunisia. Patients will be eligible for enrollment if they are aged over 35 years, are newly diagnosed with hypertension, or are known to be poorly controlled on antihypertensive therapy. Participants will be randomly assigned in a 1:1 ratio to the telemonitoring arm or usual care arm. The telemonitoring arm will involve a weekly telephone call for the collection of the home blood pressure measurements, therapeutic education, and treatment compliance assessment as well as a monthly call for treatment titration and a side effect check. Randomization will be done via the use of an interactive web responsive system, and patients will be stratified by investigation center. Neither participants nor investigators will be masked to the group assignments. The primary outcome will be the change in mean 24-hour systolic blood pressure from baseline to the 6-month follow-up in the 2 groups. All randomized patients who attend the follow-up visit at 6 months and have no missing data for the primary outcome will be included in the analysis.

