
### Research Questions

The aim of the HOROSCOPE (Home Telemonitoring of Arterial Hypertension With Antihypertensive Treatment Titration: Randomized Controlled Prospective Trial) study is to demonstrate the impact of telemonitoring on blood pressure control among patients with hypertension.

The trial will address the following three main research questions: (1) does telemonitoring improve treatment compliance and blood pressure control in newly diagnosed or poorly controlled patients with hypertension, (2) does telemonitoring improve patients’ quality of life, and (3) does telemonitoring reduce the incidence of cardiovascular complications?

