## Methods

### Study Design

Our trial will be a multicentric, rater-blinded, prospective randomized controlled trial. The allocation ratio between the intervention and control group will be 1:1. Randomization will be done via the use of an interactive web responsive system, and patients will be stratified by investigation center. Neither participants nor investigators will be masked to the group assignments. However, the cardiologist, who will interpret the results of the primary outcome, will be blinded.

The study is expected to last for an overall duration of 12 months (from the first patient who is enrolled to the last patient who completes the trial). The recruitment period will last for 6 months, and the follow-up interval will be 6 months.

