### Sample Size

A sample size of 199 subjects per group is required for 80% power, assuming a mean difference in the reduction of SBP of at least 5 mm Hg between the two study groups and an SD of 15 mm Hg. Considering a patient dropout ratio of 15%, the study will need to recruit 230 subjects in each group.

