### Statistical Analysis

Categorical variables will be expressed as frequencies and percentages, while continuous variables will be expressed as means with SDs. An analysis of variance will be performed to compare the two study groups in terms of the primary end point. The normality of continuous data will be assessed with the Shapiro-Wilk test. Furthermore, we will use a general linear model for repeated measures to compare the marginal means of Gaussian quantitative dependent variables before and after the intervention (a Bonferroni test will be considered). A nonparametric test (the Friedman test) will be used for the comparison of non-Gaussian quantitative variables before and after intervention. The Cochran Q test will be performed to compare binary dependent variables before and after intervention. Subgroup analyses will be performed by age (<65 years and ≥65 years), sex, and the severity of hypertension. Differences between continuous variables will be evaluated with a 2-tailed Student *t* test or by its correction, as appropriate. The differences among the categorical variables will be evaluated with the Pearson chi-square test. All tests will be considered significant at the cutoff value of *P*<.05.

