### Strengths and Limitations

Randomized controlled trials are considered the “gold standard for evaluating the efficacy of different interventions in clinical research and constitute evidence for medical treatment” [17]. By conducting such a trial and ensuring internal validity, we will maximize the robustness of our study.

A possible limitation is that enrolled patients may greatly vary in terms of their clinical profiles. In addition, subjects may feel overloaded by the daily measurements and questionnaires that need to be answered, which could result in dropouts. Another possible limitation is that the study population may not represent the overall Tunisian population.

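### The two entry routes that define the population (newly diagnosed, or poorly controlled on treatment) appear neither as a factor in the stated primary analysis nor among the listed subgroups

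*Protocol article*

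**What the plan says.** The Methods paragraph of the abstract admits patients who "are newly diagnosed with hypertension, or are known to be poorly controlled on antihypertensive therapy". Textbox 1 lists the same two routes, without stating there that the second group is on therapy. The first research question covers both: "does telemonitoring improve treatment compliance and blood pressure control in newly diagnosed or poorly controlled patients with hypertension".

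On allocation, the Study Design section says "patients will be stratified by investigation center" and names no other stratification factor.

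On analysis, the Statistical Analysis section compares the groups on the primary end point by analysis of variance and names no covariate. It then states: "Subgroup analyses will be performed by age (<65 years and ≥65 years), sex, and the severity of hypertension". It does not define severity.

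The Strengths and Limitations section concedes that "enrolled patients may greatly vary in terms of their clinical profiles", with no analytic response attached.

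**The concern.** A patient starting a first treatment and a patient uncontrolled on existing treatment may respond differently. In the first, starting treatment can lower pressure in both arms. In the second, telemonitoring has to work through titration and adherence. Both the average change and the telemonitoring effect could therefore differ by entry route.

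Two things are at stake. Variation explained by a characteristic known at entry stays in the residual of an unadjusted analysis. And the pooled effect is a weighted average whose weights depend on the mix the sites happen to enrol, which the article neither fixes nor predicts. A reader of the results would want to know whether the effect looks similar in the two groups. The article chose to name three subgroups, and the split used to define its own population is not one of them.

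**Working it through.** **Inputs from the article.** Sample Size section: "A sample size of 199 subjects per group is required for 80% power". The inputs behind that figure are a 5 mm Hg between-group difference in systolic reduction and SD 15; allowing for dropout raises it to 230 per group. Significance level 0.05 from Statistical Analysis, taken as two-sided.

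**Inputs assumed.** The article does not give p, the share newly diagnosed, or d, the difference in mean systolic change between the two entry groups. I use p = 30-50% and d = 5-10 mm Hg, and for power a wider share of 10-50%. SD 15 is taken as the overall SD of the change.

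**Outcome form.** The article gives the primary outcome both as a mean change (abstract) and as a percentage of patients with a 10 mm Hg change (Primary Outcome). I use the mean change, which matches the sample-size inputs and the analysis of variance.

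**The plan's own figure.** n per group = 2 × 15² × (1.96 + 0.84)² / 5², which gives 142, not 199. With 199 per group the stated inputs give about 91% power. This is a separate matter and does not bear on the present point; 199 is used below as the number analysed per group.

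**Share of variance explained by entry status** = p(1−p)d² / 15²:

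| | p = 0.3 | p = 0.5 |
|---|---|---|
| d = 5 | 0.21 × 25 / 225 = 2.3% | 0.25 × 25 / 225 = 2.8% |
| d = 10 | 0.21 × 100 / 225 = 9.3% | 0.25 × 100 / 225 = 11.1% |

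Adjustment multiplies the standard error by √(1 − share): √0.977 = 0.99 at the low end and √0.889 = 0.94 at the high end. With 230 per arm the unadjusted 95% half-width is 1.96 × 15 × √(2/230) = 2.7 mm Hg, so the best case is about 2.7 × 0.94 = 2.6 mm Hg.

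**Chance imbalance**, 95% range of the shift in the arm difference = 1.96 × √(2p(1−p)/230) × d:
- p = 0.3, d = 5: ±0.42 mm Hg
- p = 0.5, d = 10: ±0.91 mm Hg

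This lies inside the ±2.7 mm Hg above; it is not an additional error.

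**Dependence on the mix.** If the telemonitoring effect differed by 5 mm Hg between the groups (an assumption), moving the newly diagnosed share from 30% to 50% would shift the pooled effect by 0.20 × 5 = 1 mm Hg.

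**What a subgroup analysis could show.** Share f, 199 analysed per arm. Standard error of the interaction = √(2 × 225/(199f) + 2 × 225/(199(1−f))). Power for a 5 mm Hg interaction = Φ(5/SE − 1.96).

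| f | SE | Power, 5 mm Hg interaction | Interaction detectable at 80% power |
|---|---|---|---|
| 0.5 | 3.01 | 38% | 8.4 mm Hg |
| 0.3 | 3.28 | 33% | 9.2 mm Hg |
| 0.2 | 3.76 | 26% | 10.5 mm Hg |
| 0.1 | 5.01 | 17% | 14.0 mm Hg |

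The subgroup would be descriptive.

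**The case against.** Several objections stand and limit the point.

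- **A reader might infer that the first research question goes unanswered.** It does not. The question joins the two groups with *or*, asks for no separate effects, and is answered by the overall comparison.
- **A reader might infer that the split is never examined.** That cannot be known. The Ethics and Dissemination section refers to a statistical analysis plan that is not shown, and the article does not call its subgroup list exhaustive. Only the absence from the stated list is established.
- **A reader might infer that severity ignores the split.** Severity is undefined, so this cannot be checked. All that follows is that it cannot be relied on to capture entry status.
- **The baseline is late.** Table 1 places the ambulatory recording at day 29 and collects compliance and side effects at the same visit. If newly diagnosed patients are already on treatment by then, part of the first-treatment fall precedes the baseline and d is smaller. The article does not say when their treatment starts.
- **The harm is small.** Randomisation keeps the comparison unbiased, chance imbalance is already in the ordinary error, and if SD 15 is the overall SD the sample size already allows for this heterogeneity.
- **The interaction has low power.** True, but for equal group shares the age, sex and severity subgroups face the same limit and are planned anyway. This argues for an estimate with an interval, labelled exploratory. It does not count against using status as a covariate.

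**Conclusion.** A modest improvement to a stated analysis, not the correction of an error or contradiction. The article defines its population by two entry routes, and its stated primary analysis and subgroup list leave that split out. The consequence is a possible loss of precision and a pooled effect that is harder to interpret, without bias.

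Under the assumed 30-50% share and 5-10 mm Hg difference, entry status explains about 2-11% of the variance of the change, which is at most about a 6% reduction in the standard error (1 − 0.94). The figure falls if treatment starts before day 29. The share and the difference are both assumptions; the article supplies neither.

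**What to change.** Before analysis, add entry status (newly diagnosed, or poorly controlled on treatment) as a factor in the primary model. Pre-specify it also as an exploratory subgroup, reporting the effect in each group and the treatment-by-status interaction estimate with its confidence interval. State that power is low: about 17-38% for a 5 mm Hg interaction over assumed shares of 10-50%.

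No change to stratification is proposed. Recruitment began in July 2020 for an expected 6 months or so, and data collection was due to finish by the end of 2021, so randomisation is almost certainly complete.

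The cost is analysis-plan wording, one degree of freedom and one more exploratory subgroup. No new data should be needed, since entry status should be known from the eligibility check and the history taken at inclusion.

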### Outcomes

#### Primary Outcome

Our primary outcome will be the percentage of patients who exhibit a change of 10 mm Hg in average 24-hour SBP from baseline to the 6-month follow-up.

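### The protocol states two incompatible primary outcomes, mean change in 24-hour SBP and percentage of patients with a 10 mm Hg change, and the sample size statement is not reproduced for either

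*Protocol article*

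**What the plan says.** The Abstract (Methods) states: "The primary outcome will be the change in mean 24-hour systolic blood pressure from baseline to the 6-month follow-up in the 2 groups". That is a continuous outcome. The Primary Outcome section states: "Our primary outcome will be the percentage of patients who exhibit a change of 10 mm Hg in average 24-hour SBP". That is a proportion. It does not say whether the change must be a fall, or whether 10 mm Hg is a minimum.

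The Sample Size section plans 199 patients per arm at 80% power. The effect behind that number is worded as follows: "assuming a mean difference in the reduction of SBP of at least 5 mm Hg between the two study groups". The standard deviation is put at 15 mm Hg, and recruitment is raised to 230 per arm to allow for 15% dropout. The section gives no responder percentage for either arm.

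The Statistical Analysis section assigns the test: "An analysis of variance will be performed to compare the two study groups in terms of the primary end point". It also names the Pearson chi-square test for categorical variables in general, without linking it to the primary end point. The overall significance cutoff is 0.05, and the t test is described as 2-tailed.

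**The concern.** Both definitions are current text, and each claims to be the primary outcome. They can give different answers from the same data: a significant difference in means with a non-significant difference in responder percentages, or the reverse. While both stand, the document does not fix which result is the headline, and that choice could be made after the results are known.

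The rest of the design does not settle the matter cleanly. The sample size inputs and the named test point to the mean, but the section that formally defines the outcomes gives the percentage. Splitting a continuous measure at a threshold also loses information, so a sample size justified for the mean cannot be assumed to serve the percentage.

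**Working it through.** **Inputs.** From Sample Size: difference 5 mm Hg, SD 15 mm Hg (taken as the SD of the change), 80% power, 199 per arm, 230 recruited per arm. From Statistical Analysis: significance level 0.05, taken as two-sided. From Study Design: 1:1 allocation.

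**Step 1: the plan's own figure, for the mean.**

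n per arm = 2 × (1.960 + 0.842)² × 15² / 5² = 141.3, rounded up to 142. The t-based calculation gives 142.2. The stated 199 is not reproduced.

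Two-sided variants give 190 (90% power), 234 (95% power), 172 (alpha 0.025) and 211 (alpha 0.01). One-sided testing at 95% power gives 195, which is close to 199 but contradicts both the stated 80% and the 2-tailed test. To obtain 199 at 80% power, the SD would have to be about 17.8 mm Hg or the difference about 4.2 mm Hg.

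Power at 199 per arm: standard error = 15 × √(2/199); 5 / standard error = 3.325; power = Φ(3.325 − 1.960) = 0.914.

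**Step 2: the percentage, under the same 5 mm Hg and SD 15.** The documents give no responder rates, so these are assumptions: changes are normal with common SD 15, telemonitoring shifts the mean fall by exactly 5 mm Hg, and a responder has a fall of at least 10 mm Hg. For a control mean fall c:

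- control responders = 1 − Φ((10 − c)/15)
- telemonitoring responders = 1 − Φ((5 − c)/15)

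Power and n come from the usual two-proportion formula (pooled variance under the null, no continuity correction).

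| Control mean fall, mm Hg | Responders, control vs telemonitoring | Power at 199 per arm | n per arm for 80% |
|---|---|---|---|
| −5 | 15.9% vs 25.2% | 64.0% | 290 |
| 0 | 25.2% vs 36.9% | 71.4% | 245 |
| 5 | 36.9% vs 50.0% | 75.0% | 226 |
| 7.5 | 43.4% vs 56.6% | 75.4% | 223 |
| 10 | 50.0% vs 63.1% | 75.0% | 226 |
| 12 | 55.3% vs 68.0% | 74.0% | 231 |
| 15 | 63.1% vs 74.8% | 71.4% | 245 |
| 20 | 74.8% vs 84.1% | 64.0% | 290 |

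The best case is c = 7.5, where the responder difference is 13.2 percentage points. Worked for that row: n = (1.3859 + 0.5899)² / 0.1324² = 222.8, rounded up to 223. No control mean reaches 80% at 199 per arm.

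**Step 3: the undefined direction.** If a change of at least 10 mm Hg in either direction counted, the same model gives about 7% power at c = 0, 24% at 5, 44% at 10 and 54% at 15 or 20. The missing direction therefore matters more than the choice of control mean.

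**Step 4: if nobody drops out.** With all 230 per arm evaluable and a responder defined by a fall, power is 80.8% at c = 5 or 10 and at most 81.2%. It is 77.5% at c = 0. The plan itself expects 15% dropout (230 × 0.85 = 195.5 per arm), and the Abstract restricts the analysis to patients with complete primary outcome data.

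**The case against.** The strongest reply is that the shortfall for the percentage is not a property of the plan but of an added model. The protocol gives no responder rates, and its 5 mm Hg is a minimum. On the same model a 5.5 mm Hg shift gives about 80-83% power at 199 per arm over control falls of 0-12 mm Hg. This stands, and the 71-75% must carry its assumptions.

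A reader might also infer that the trial has no valid sample size. The documents do not support that. Under the stated model the gap is about 5 to 9 points for control falls of 0-12 mm Hg, and for the mean the planned number is more than its inputs require.

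A reader might infer that the analysis of variance would be a damaging error for a yes/no outcome. With two arms it is nearly the chi-square test: for 73/199 vs 100/199 responders the p-values are 0.0062 and 0.0063. Its naming shows that a continuous outcome was in mind, and little more.

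It could be said that an article condenses a fuller protocol. That excuses omissions, but not two different statements of the primary outcome.

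**Conclusion.** The contradiction is certain and rests on the text alone. The sample size inputs and the test assigned to the primary end point are of the mean type, so the mean change is the version the design supports best. Even so, the pairing of 199 per arm with 80% power is not reproduced for either outcome: the mean has about 91% power at 199 and needs about 142 for 80%.

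For the percentage, power is about 71-75% over control falls of 0-12 mm Hg (64% at −5 or 20), and about 223-245 per arm would be needed over the 0-12 range. This holds only for normal changes, SD 15, a shift of exactly 5 mm Hg, 199 evaluable per arm and a responder defined as a fall of at least 10 mm Hg. It should not be read as an established loss of power. Nor do the documents show that an outcome was chosen or changed after seeing data; they only leave room for it.

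**What to change.** 1. Name one primary outcome in the Abstract, Outcomes, Sample Size and Statistical Analysis sections: the between-arm difference in mean change in 24-hour SBP from the pre-randomisation ABPM (day 29 in Table 1) to month 6.
2. Document when this was settled and that it was settled without sight of comparative results. Recruitment began in July 2020, data collection was expected to finish by the end of 2021 and the article appeared in March 2022, so the record matters.
3. Move the responder percentage to secondary, defined as a fall of at least 10 mm Hg in average 24-hour SBP and compared as a proportion.
4. Correct the sample size statement: either report about 91% power at 199 per arm for the stated 5 and 15 mm Hg, or give the missing input that leads to 199 at 80%.

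The cost is a wording change and a dated record of the decision. The ABPM is already scheduled at both time points, so no extra patients, visits or data are needed.

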#### Secondary Outcomes

The following will be our secondary outcomes:

The percentage of patients who exhibit a change of 5 mm Hg in average 24-hour diastolic blood pressure from baseline to the 6-month follow-upThe percentage of patients who exhibit a change of 10 mm Hg and 5 mm Hg in average 24-hour blood pressure from baseline to the 6-month follow-upThe change in blood pressure load (Textbox 2) percentages from baseline to the 6-month follow-upThe change in dipping (Textbox 2) percentages from baseline to the 6-month follow-upThe percentage of patients taking more than 80% (400/500) of the antihypertensive medications at the 6-month follow-upThe percentage of patients with changes in mean 12-Item Short Form Survey scores from baseline to the 6-month follow-upClinical outcomes, including hospitalization rates and emergency room admissions related to high blood pressure, adverse effects, or other reasons

Blood pressure load and dipping definitions.
**Definitions**
Blood pressure load: the percentage of abnormally elevated blood pressure readings, which is usually provided in the ambulatory blood pressure monitoring report. Normal values should be <40% [14,15].Dipping: the difference between the mean systolic pressure during the day and mean systolic pressure during the night. This is expressed as a percentage of the daytime mean, and the accepted normal ranges between 10% and 20% [16].

### Ethics and Dissemination

Full ethical approval for the trial was obtained from the local ethics committee of Monastir University of Medicine (reference number: IORG 0009738 N° 50/098060279). The study is registered on the ClinicalTrials.gov registry under the identifier NCT04607239.

The electronic data capture system that was provided to the study is compliant with confidentiality requirements (ie, those of the US FDA Title 21 of the CFR, part 11; HIPAA, ICH; and GDPR), and local regulatory authorization was obtained before starting the project. Personal data that are not relevant to the study will not be collected. Other personal data will be secured by obtaining specific rights for their use in follow-up monitoring only. Investigators and research associates will sign a confidentiality agreement before starting the project.

The final data set will be extracted from the electronic data capture system along with anonymized personal data. The primary investigator will be responsible for access to the final data set for medical writing purposes. The Contract Research Organization team of Dacima is authorized to access the final data set to program statistical analyses and provide the final results of the project according to the statistical analysis plan. The primary investigator will be responsible for reviewing the data analysis and validating the final clinical study report.

## Results

Recruitment to the trial started in July 2020. The data collection period is expected to last for approximately 12 months (from the first patient who is enrolled to the last patient who completes the trial). The length of the study per patient will be 6 months. We expect to complete data collection by the end of 2021 and plan to disseminate the results subsequently.

